## Abstract

**Background:**

Exclusive breastfeeding for the first 6 months of life is the optimal way to feed infants. However, recent studies suggest that exclusive breastfeeding rates in China remain low and are well below the recommended target. There has been evidence that a lack of awareness of, or exposure to, breastfeeding information is associated with poor breastfeeding practices. WeChat, the most widely used social networking platform in China, has shown some potential to promote health behaviours. We thus hypothesised that a breastfeeding intervention program delivered via WeChat would achieve at least a 10% increase in exclusive breastfeeding prevalence at 6 months compared to the control group.

**Methods:**

A two-arm, parallel, multicentre randomised controlled trial of 1000 pregnant women will be conducted at four maternity hospitals of Chengdu, China. Eligible women who consent to participate in the trial will be recruited at 28–30 weeks of gestation, and randomly allocated to either the intervention group (participants receive breastfeeding-related information from WeChat) or the control group (participants receive non-breastfeeding information from WeChat) using a central randomisation system on a 1:1 ratio at each participating site. The primary outcomes are exclusive breastfeeding rate and full breastfeeding rate at 6 months postpartum. All randomised participants will be included in the outcome analyses with missing data being imputed based on the best-case and worst-case scenarios. Multilevel mixed regression models will be used in the primary analyses to assess the effectiveness of intervention program on the breastfeeding rates.

**Discussion:**

This trial uses the most widely used social media program as a means of delivering messages to mothers to increase exclusive breastfeeding in China. Increasing exclusive breastfeeding will contribute to meeting the health and environmental goals of the Sustainable Development Guidelines.

*Trial registration* ClinicalTrials.gov, NCT04499404. Registered 5 August 2020—Retrospectively registered, https://clinicaltrials.gov/show/NCT04499404

## Background

Breastfeeding is known to provide both short-term and long-term benefits to infants, mothers and the society in general [1, 2]. Both the World Health Organization (WHO) and the Chinese Ministry of Health recommend that infants should be exclusively breastfed for the first 6 months of life to achieve optimal growth, development and health [3]. Exclusively breastfed infants have a reduced risk of infectious diseases such as diarrhoea, and pneumonia, and are less likely to develop obesity and diabetes in later life [4–6]. Many studies have also confirmed that breastfeeding is associated with improved performance in intelligence tests during childhood and adolescence [7].

Despite the majority of Chinese infants are initially breastfed for at least one feed, the exclusive breastfeeding rate at 6 months falls significantly below ideal levels [8, 9], with infant formula being widely used in both rural and urban China [10, 11]. According to a report from UNICEF, only 20.8% of Chinese infants were exclusively breastfed within the first 6 months of life in 2013 [12]. A recent survey undertaken across China during 2017–2018 shows that the rate of exclusive breastfeeding remains low, with less than 30% of infants aged 0–6 months being exclusively breastfed [13]. Given the high prevalence of infant formula use and related health problems, every effort is needed to improve breastfeeding practices in China to meet the recommended target.

Previous research has identified a wide range of sociodemographic, biophysical, psychosocial and cultural factors associated with breastfeeding practices, including a lack of awareness to information that promote and supports breastfeeding [14, 15]. Education and improving access to skilled lactation counselling have been shown to increase exclusive breastfeeding rates by 90% [16].

Many studies have suggested to deliver breastfeeding education and related information via the internet or mobile phone short messages service (SMS) to improve breastfeeding outcomes. For instance, in a quasi-experimental cohort study of 582 women in Shanghai, the median duration of exclusive breastfeeding and exclusive breastfeeding rate at 6 months postpartum were significantly increased in the intervention group who received infant feeding messages delivered by SMS [17]. A systematic review and meta-analysis showed that women who received antenatal interventions using SMS/mobile phone were more likely to initiate breastfeeding within 1 hour after childbirth and less likely to stop exclusive breastfeeding before 6 months compared to women who received routine care [18].

Alongside the rapid development of internet and information technology, social media and smartphones have been widely used in health education research and have shown potential in improving health behaviours [19, 20]. WeChat, a free smartphone application, is the most frequently and widely used social networking platform in China. According to a report from Tencent, Inc., the developer of WeChat, its monthly-active-user reached 1.16 billion in the last quarter of 2019. Besides instant text messaging and free audio/video calls, WeChat provides many other daily living services including mobile payment, browsing and posting information sharing on moments, sending red envelops and pay utility bills [21]. As comparable to Facebook pages, WeChat public accounts can send push notifications to their followers and alert them to new content.

Due to its convenience and availability, WeChat has become a new medium and tool for health information dissemination, with great potential to affect the general public’s health behaviours. Compared to mobile phone SMS, WeChat public accounts are able to deliver health education messages in a cheaper and more visual, enjoyable way. Some studies conducted in China showed that WeChat platform is effective in health promotion interventions [22, 23]. In addition, the use of online health counselling services, including WeChat-based resources, becomes particularly popular under the coronavirus disease 2019 (COVID-19) outbreak in China [24]. However, to our knowledge, no studies have been conducted to investigate the effectiveness of a WeChat-based intervention to promote breastfeeding practices.

We have designed a randomised controlled trial (RCT) for a breastfeeding intervention program using WeChat in urban China to increase exclusive breastfeeding rates. Our hypothesis is that the intervention program will lead to at least a 10% increase in exclusive breastfeeding prevalence at 6 months when compared to the control group.

## Methods

### Study design and setting

A two-arm, parallel RCT of 1000 participants (500 in each arm) will be conducted at four maternity hospitals in Chengdu, China. Chengdu, the capital of Sichuan Province, is located in southwest China with a population of 15.9 million. According to the National Bureau of Statistics, the disposable annual income per capita of urban residents in Chengdu was 42,128 RMB in 2018, slightly higher than the average national level of 39,251 RMB.

Eligible pregnant women who consent to participate will be recruited from the antenatal clinic of the four maternity hospitals between 28 and 30 weeks of gestation and will be randomly assigned to either the intervention or control group via a central randomisation system on a 1:1 ratio at each participating site. Based on their number of live births in 2018, a total of 300, 300, 200 and 200 women will be recruited, respectively, from Chengdu Women's and Children's Central Hospital, Chengdu Jinjiang Maternity and Child Health Hospital, Chengdu Qingyang Maternal and Child Health Hospital, and Chengdu Wuhou Maternal and Child Health Hospital. Participants recruitment started in June 2020 and is expected to end in May 2021. We followed the Standard Protocol Items: Recommendations for Interventional Trials (SPIRIT) guidelines for developing our trial protocol [25, 26]. The design of the RCT is summarized in Fig. 1.

**Fig. 1. Fig1:**
[figure not shown]
Flow diagram of the RCT

### Participants and recruitment

Pregnant women meeting the following inclusion criteria will be invited to participate in the study: (1) 18 years or above, (2) own a smartphone, (3) carry a singleton fetus, (4) at a gestational age of 28 to 30 weeks, and (5) have sufficient language skills (i.e. completed secondary school education).

Pregnant women will be excluded from the study if they meet either of the following criteria: (1) have existing medical conditions or pregnancy complications which may inhibit breastfeeding initiation, according to their medical doctor, (2) intend to give birth in health institutes other than the study hospitals.

The aims of the study (i.e. to improve maternal and child health) and participants’ right to withdraw at any time will be explained to potentially eligible women both verbally and via an information sheet. The consent form will be completed and signed by the participants prior to recruitment.

### Randomisation and baseline data collection

Eligible pregnant women consenting to participate in the study will be randomly assigned via a central randomisation system to an intervention group (participants receive breastfeeding-related information from WeChat) or a control group (participants receive non-breastfeeding information from WeChat) at an allocation ratio of 1:1. We will perform block randomisation within each participating hospital, with varying block sizes of 4 or 6.

After randomisation, a trained nurse who is not aware of the group allocation will conduct face-to-face interview of the consented participant using a structured questionnaire (Additional file 1) to collect information on sociodemographic and health characteristics, and lifestyle (cigarette smoking and alcohol drinking). Information on maternal attitudes towards infant feeding will be solicited using the Chinese version of the Iowa Infant Feeding Attitude Scale [27]. Self-reported data on height and weight before pregnancy will also be collected at baseline interview.

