### Statistical analysis

Descriptive statistics will be performed to summarise participants’ baseline characteristics and the outcome variables. Independent t-tests or Mann–Whitney U tests will be performed to compare continuous variables and chi-square or Fisher’s exact tests to compare categorical characteristics.

Kaplan–Meier curves and log-rank test will be used to compare breastfeeding duration between the intervention and control groups. The Cox proportion hazards model will be conducted to determine the hazard ratios of exclusive and any breastfeeding cessation, accounting for baseline characteristics and other plausible factors associated with breastfeeding practices. Similar analyses will be applied to analyse the data of complementary foods introduction. Multilevel mixed regression models will be used to assess the effectiveness of intervention program on breastfeeding rates at four and 6 months.

We will follow the intention-to-treat principle with all randomised participants included in the analysis, and the missing data will be imputed based on the best-case and worst-case scenarios. Subgroup analyses will be conducted according to variables of interest.

QSR International NVivo 11 software will be used to perform qualitative analysis. The focus group discussions and in-depth interviews will be transcribed verbatim and inductive thematic analysis will be applied to analysis of the transcripts from process evaluation and the exit interviews.

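### The log-rank test is not stratified by hospital, the randomisation stratum, and the primary model names no baseline covariate although an attitude score is collected: valid, but slightly imprecise and free to improve

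*Protocol article*

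**What the plan says.** On allocation, the section Randomisation and baseline data collection states: "We will perform block randomisation within each participating hospital, with varying block sizes of 4 or 6", "at an allocation ratio of 1:1". Under Study design and setting, "a total of 300, 300, 200 and 200 women will be recruited" from the four hospitals.

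On baseline data, the same randomisation section states: "Information on maternal attitudes towards infant feeding will be solicited using the Chinese version of the Iowa Infant Feeding Attitude Scale". A nurse unaware of the allocation does this interview after randomisation. According to Interventions, women follow the WeChat account only once the interview is over.

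On analysis, the Abstract (Methods) says: "Multilevel mixed regression models will be used in the primary analyses to assess the effectiveness of intervention program on the breastfeeding rates". The Statistical analysis section repeats this: "Multilevel mixed regression models will be used to assess the effectiveness of intervention program on breastfeeding rates at four and 6 months". Neither place names the levels of the model or any covariate. For duration, the plan is that a "log-rank test will be used to compare breastfeeding duration between the intervention and control groups", with no mention of hospital. The Cox model for cessation, described next, is to be adjusted for baseline characteristics and other factors.

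**The concern.** A factor that restricts the randomisation should also appear in the analysis. Blocking within hospital balances the arms on hospital. If outcomes differ between hospitals and the analysis ignores this, the standard error still contains between-hospital variation that the design has removed. The test is then a little conservative.

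A prognostic baseline measure is a second source of precision that is already paid for. The attitude score is a legitimate covariate, because it is taken by a masked interviewer before any message arrives. The article itself makes it plausible that the score is prognostic: the Background lists psychosocial factors among the correlates of breastfeeding, and the Discussion links misconceptions about infant feeding to formula use. Yet adjustment is described for the supporting Cox model and not for the model called primary.

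What is at stake is some precision on a 10-point difference, and the freedom to choose covariates later if none is named in advance. Bias is not at issue.

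**Working it through.** **1. The plan's own figure.** Inputs from Sample size: 25% against 35%, two-sided 5%, power 90%. With the standard pooled form,

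n = {[1.960 × √(2 × 0.30 × 0.70) + 1.2816 × √(0.25 × 0.75 + 0.35 × 0.65)] / 0.10}² = {[1.2702 + 0.8256] / 0.10}² = 439.2, so 440 per arm and 880 in total.

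This agrees with the stated 890 (450 per group) to within 3%. Power is 0.907 at 450 per arm. That is the base for what follows.

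**2. What had to be assumed.** The documents give neither the between-hospital spread in exclusive breastfeeding nor the strength of the attitude score. Assumed ranges: hospital SD on the log-odds scale 0 to 0.6; log odds ratio per SD of the score 0 to 0.6.

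**3. Simulation.** There were 900 evaluable women (the recruitment targets less 10%: 270, 270, 180, 180), with arms balanced within hospital and overall rates of 25% and 35%. Logistic regression was run on 3000 replicates per scenario. The three analyses were no covariates, hospital as a fixed effect, and hospital plus score. Gains are in percentage points, from unrounded results.

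| Hospital SD | Score log-OR | Neither | Hospital | Hospital + score | Gain from score, hospital already in | Gain from both |
|---|---|---|---|---|---|---|
| 0 | 0 | 0.908 | 0.908 | 0.909 | 0.1 | 0.1 |
| 0 | 0.3 | 0.906 | 0.906 | 0.908 | 0.2 | 0.3 |
| 0 | 0.6 | 0.907 | 0.907 | 0.923 | 1.6 | 1.7 |
| 0.2 | 0 | 0.903 | 0.905 | 0.905 | 0.0 | 0.2 |
| 0.2 | 0.3 | 0.907 | 0.908 | 0.915 | 0.7 | 0.8 |
| 0.2 | 0.6 | 0.903 | 0.905 | 0.926 | 2.1 | 2.3 |
| 0.4 | 0 | 0.907 | 0.911 | 0.911 | −0.1 | 0.4 |
| 0.4 | 0.3 | 0.912 | 0.919 | 0.919 | 0.0 | 0.7 |
| 0.4 | 0.6 | 0.910 | 0.914 | 0.932 | 1.8 | 2.3 |
| 0.6 | 0 | 0.919 | 0.931 | 0.929 | −0.2 | 1.0 |
| 0.6 | 0.3 | 0.904 | 0.920 | 0.923 | 0.3 | 1.9 |
| 0.6 | 0.6 | 0.908 | 0.919 | 0.935 | 1.6 | 2.7 |

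The Monte Carlo standard error of one power figure is about √(0.91 × 0.09 / 3000) = 0.005. The small negative gains are noise.

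Hospital alone adds about 0 to 1.6 points. The score adds about 0 to 2.1 on top of hospital. Both together add about 0 to 2.7.

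**4. Validity.** Under no effect, the rejection rate was 0.040 to 0.054 without covariates and 0.040 to 0.056 with them. At hospital SD 0.6, ignoring hospital gave 0.041, 0.040 and 0.046 across the three score strengths, against 0.047, 0.046 and 0.053 with hospital in the model. This is the mild conservatism expected after blocked randomisation.

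**5. Log-rank test.** No separate figure was computed. The same reasoning applies: the unstratified test is valid and at most slightly conservative if hospitals differ.

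**The case against.** The strongest reply is that this reads silence as a plan. The document is a condensed article, and a covariate list is commonly left to the full protocol or analysis plan. That stands. A reader might infer that the primary model leaves out hospital and the score, but the text does not say so. Hospital is the only clustering unit in the design besides repeated visits, so a multilevel model most plausibly already has it as a level. What remains is that the same section names adjustment for the Cox model and none for the primary one.

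A reader might also infer that a random effect with four levels will often be estimated at zero and so lose the stratum. Under an approximation on the log-odds scale (225 women per hospital, 30% rate), a zero estimate occurs in about 56% of trials at a true SD of 0.1, but in only 7% at 0.4. With assumed hospital rates of 15, 25, 30 and 35%, the 3-df heterogeneity statistic has noncentrality (270 × 0.10² + 180 × 0.05² + 180 × 0.10²) / (0.25 × 0.75) = 4.95 / 0.1875 = 26.4, and the chance of a zero estimate is about 0.0001. The effect drops out mainly when there is little to lose. Fixed or random hospital is a matter of preference here.

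A third tempting reading is that the Cox model ignores hospital. Its adjustment wording is broad enough to cover both hospital and the score. All that can be said is that no stratification is stated.

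Finally, the log-rank test serves a secondary outcome and stands beside an adjusted Cox model, so it does not touch the primary result. That also stands, and it limits the weight of the point.

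**Conclusion.** The point holds as a minor, free improvement. The stated log-rank test does not use the randomisation stratum, and the stated primary model names no baseline covariate although a suitable one is collected. Followed as written, the analysis is valid and the trial keeps its planned power of about 90% at 450 per arm.

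The loss is about 0 to 2.1 points of power if hospital is already a level of the primary model, and about 0 to 2.7 points if it is not. Both ranges rest on assumed hospital spread and score strength. A larger gain can be obtained by assuming that hospital and score explain 5 to 15% of the outcome variance and dividing 450 by one minus that share: power then becomes 0.920 to 0.945, or 1.3 to 3.8 points above 0.907. The documents do not support those shares, and the conversion is a linear-model shortcut for a binary outcome, so the simulated range is preferred.

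**What to change.** Three changes of wording in the Statistical analysis section, or in the analysis plan before unblinding:

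- Stratify the log-rank test by hospital.
- State that hospital enters the primary model and the Cox model, and in what form: fixed effect, random level or stratum. Any of these will do.
- Name the baseline attitude score in advance as a covariate in the primary 6-month model.

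If the link is logistic, say also that the adjusted odds ratio is conditional on the score, so that it is not read as the unadjusted contrast.

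The cost is wording only: no new data, visits or participants. Hospital as a fixed effect uses 3 degrees of freedom out of about 900.

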### Interventions

Immediately after baseline interview, all participants will be asked to scan a Quick Response (QR) code to follow our WeChat public account named ‘Chengdu Maternal and Child Health Information eCard Management System’, which will send push notifications to alert the participants for new content, topics, and frequently asked questions and answers (Fig. 2). In order to minimise potential contamination, the messages are visible to our study participants only and the information forwarding function is disabled. In addition, participants are told not to share the messages with others in ways such as screenshot.

**Fig. 2. Fig2:**
[figure not shown]
Examples of pushed content (**a** example of pushed content for the intervention group; **b** example of pushed content for the control group). The image depicted in figure is our own.

From baseline (30 weeks of gestation) until childbirth, the intervention group participants will receive breastfeeding related messages (one message each time, three times a week) from WeChat, including preparation for breastfeeding after birth and the health benefits of breastfeeding, whereas the control group women will receive messages mainly on topics of healthy lifestyle and nutrition during pregnancy. Before delivery, there are ten messages for each group and the repeat cycle is 3 weeks.

After childbirth, mothers in the intervention group will continue to receive information, which is mainly about breastfeeding, twice a week (one message each time) for 6 months. We will use WeChat to remind mothers about the importance of exclusive breastfeeding, build confidence and motivate them to continue exclusive breastfeeding. Meanwhile, the control group mothers will receive information mainly on routine parental care, such as immunization, safety, and infant growth. The dose and frequency of messages are the same as the intervention group. We developed the intervention content based on literature review, expert consultations and focus group discussion among pregnant and postpartum women. Every participant receives regular prenatal and postpartum maternity services. All the messages are presented in the Additional file 2.

### Formative research focus groups

Two focus groups, one with ten pregnant women and another with ten postpartum mothers, were undertaken to pilot test the intervention content and questionnaires before the implementation of the trial. These research materials have been modified based on the feedbacks to ensure their contents are relevant and appropriate to the target group.

### Follow-up and outcomes

After childbirth, information on maternal weight gain during pregnancy, obstetric complications and neonatal and pregnancy outcomes, such as delivery method, birthweight and infant gender, will be extracted from medical records. Each participant will be interviewed in person by trained nurses at discharge and be interviewed by telephone at 1, 4, and 6 months postpartum to collect detailed information on breastfeeding practices. Information gathered from the participants will be entered into tablet computers during the interviews. Preliminary logic and range checks are built into the data entry system. Data will be saved locally and synchronized to server once the device is connected to an internet connection. The questionnaires used (Additional file 1) are taken from our previous studies conducted in Sichuan Province [28, 29], whose validity has been verified for Chinese mothers.

#### Primary outcomes

The primary outcomes are exclusive breastfeeding rate and full breastfeeding rate at 6 months postpartum. We follow the WHO’s definition of exclusive breastfeeding as “Breastfeeding while giving no other food or liquid, not even water, with the exception of drops or syrups consisting of vitamins, mineral supplements or medicines” [30]. Full breastfeeding is defined as “Infants who are receiving almost all of their nutrients from breast milk but take some other liquids such as water, water-based drinks, oral rehydration solutions, ritual fluids, and drops or syrups” [31].

To obtain information on infant feeding practices at 6 months, mothers will be asked the following two questions: (1) How did you feed your baby in the past 24 h? The response options are: “Breastfeeding only”, “Breastfeeding + water/glucose water/fruit juice”, “Mainly breastfeeding but ‘topping up’ with infant formula”, “Mainly infant formula but also breastfeeding”, and “Infant formula only”; (2) Did you give complementary foods to your baby in the past 24 h? If the response is ‘Yes’, mothers will be asked to provide the name of each complementary food. In our study, complementary feeding is defined as feeding infants with solid foods and liquids other than breastmilk or infant formula [32].

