### Sample size

Exclusive breastfeeding rates at 6 months postpartum (the primary outcome variable) and the sample size of the study was determined using the formula as follows [33]:$${\text{n}} = \left\{ {\frac{{{\text{Z}}_{{\alpha /2}} \sqrt {{\text{P}}_{{\text{e}}} \left( {1 - {\text{P}}_{{\text{e}}} } \right)} + {\text{Z}}_{{\beta /2}} \sqrt {{\text{P}}_{1} \left( {1 - {\text{P}}_{1} } \right) + {\text{P}}_{2} (1 - {\text{P}}_{2} )} }}{{{\text{P}}_{1} - {\text{P}}_{2} }}} \right\}^{2}$$

where n is the required sample size for each group; Z_α/2_ and Z_β/2_ are the critical Z values for a given alpha and beta level respectively; P_1_ and P_2_ are the estimated exclusive breastfeeding rates at 6 months in the control and intervention group, respectively; P_e_ = P_1_ × 0.50 + P_2_ × 0.50.

Based on the results of our recent prospective cohort conducted in Chengdu [34], we assume that the exclusive breastfeeding rate for mothers in the control group is P_1_ = 25% at 6 months. In addition, we hypothesize a conservative effect size of 10% improvement in the exclusive breastfeeding rate for the intervention group relative to the control group (P_2_ = 35%). The estimated sample size is 890 (450 per group) under a power of 90% and a two-sided significance level of 5%. Taking into account a loss to follow-up of 10%, the total sample size required at baseline for the RCT is 1000 (500 per group). It was assumed that approximately 20% of women will decline to participate, especially due to the COVID-19 pandemic, we therefore plan to approach about 1250 women at the four hospital antenatal clinics.

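### Two primary outcomes are declared, but the hypothesis and the sample size rest on exclusive breastfeeding alone, so the protocol is inconsistent about which result decides the trial

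*Protocol article*

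**What the plan says.** The Primary outcomes section, and the Methods part of the Abstract in the same words, declare two: "The primary outcomes are exclusive breastfeeding rate and full breastfeeding rate at 6 months postpartum".

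Elsewhere there is one. The hypothesis, in the Abstract and again at the end of the Background, is "at least a 10% increase in exclusive breastfeeding prevalence at 6 months when compared to the control group". The Sample size section opens with "Exclusive breastfeeding rates at 6 months postpartum (the primary outcome variable", in the singular, and sizes the trial on it: "we assume that the exclusive breastfeeding rate for mothers in the control group is P_1_ = 25% at 6 months", with a 10-point gain "relative to the control group (P_2_ = 35"%), "under a power of 90% and a two-sided significance level of 5"%. The result is "The estimated sample size is 890 (450 per group"), raised to 1000 enrolled for 10% loss.

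For full breastfeeding the article gives a definition, but no expected rate, effect or power. It is not in the list of secondary outcomes either. The Statistical analysis section names one type of model for the breastfeeding rates at 4 and 6 months and does not say how the two primary results combine.

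**The concern.** A published protocol should let a reader tell in advance which result will make the trial positive. Here the outcome sections give full breastfeeding equal standing with exclusive breastfeeding, while the hypothesis and the sizing give it none.

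The two outcomes come from the same two feeding questions and differ only in whether other liquids were given. It is quite possible for one to reach significance and the other not. A report could then lead with either and cite this article in support. The 5% and 90% in the Sample size section describe one comparison. Whether they also describe the trial depends on how the second primary outcome is treated.

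**Working it through.** **Inputs from the article.** Exclusive breastfeeding 25% (control) and 35% (intervention), two-sided 5%, 90% power, 1:1 allocation, 450 per group evaluable, 10% loss.

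**Inputs the article does not give (assumptions).** The full-breastfeeding rates, the gain in them, and the correlation between the two tests. Ranges are shown.

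**1. The plan's own figure.** The standard two-proportion formula, with mean rate 0.30, is

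n = {[z(α/2)·√(2 × 0.30 × 0.70) + z(β)·√(0.25 × 0.75 + 0.35 × 0.65)] / 0.10}²
= [(1.960 × 0.6481 + 1.2816 × 0.6442) / 0.10]² = 439.2,

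so 440 per group and 880 in total, close to the stated 890. (The formula as printed lacks the factor 2 under the first root and uses Z_β/2; it gives 384 per group, so the stated size matches the standard form.) At 450 per group, power = Φ[(0.10 × √450 − 1.960 × 0.6481) / 0.6442] = Φ(1.321) = 90.7%. The sizing holds for exclusive breastfeeding alone.

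**2. Rule "either": success if either outcome reaches 5%.** With no effect on either outcome, the family-wise error is 1 − P(|Z₁| < 1.96 and |Z₂| < 1.96) for a bivariate normal pair with correlation ρ. Take exclusive breastfeeding at p_E = 0.25 and full breastfeeding at p_F.

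If exclusive is counted within full (nested), ρ = √{p_E(1 − p_F) / [p_F(1 − p_E)]}. If the printed definition is read literally, infants who take other liquids form a separate category, and ρ = −√{p_E·p_F / [(1 − p_E)(1 − p_F)]}.

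| Reading | Assumed p_F | ρ | Family-wise error |
|---|---|---|---|
| Nested | 30% | 0.88 | 7.2% |
| Nested | 35% | 0.79 | 7.9% |
| Nested | 40% | 0.71 | 8.3% |
| Mutually exclusive | 5% | −0.13 | 9.7% |
| Mutually exclusive | 10% | −0.19 | 9.7% |
| Mutually exclusive | 15% | −0.24 | 9.6% |

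Independent tests would give 1 − 0.95² = 9.75%. Power to detect at least one effect is not reduced under this rule.

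**3. Rule "both": success only if both reach 5%.** The type I error stays at or below 5%. Joint power at 450 per group, nested reading, with an assumed 10-point gain in full breastfeeding and ρ taken at the pooled rates:

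| Assumed full rate, control | Power, full alone | ρ | Power for both |
|---|---|---|---|
| 30% | 88.3% | 0.89 | 86.0% |
| 35% | 86.6% | 0.80 | 83.6% |
| 40% | 85.6% | 0.72 | 82.0% |
| 50% | 85.6% | 0.59 | 80.9% |

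If instead each test had 90.7% power, joint power would be 82.2% at ρ = 0 and 87.7% at ρ = 0.9. The range is about 81 to 88%.

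**4. Rule "split": Bonferroni, two-sided 2.5% each.** With z = 2.2414, power for exclusive breastfeeding at 450 per group is Φ[(2.1213 − 2.2414 × 0.6481) / 0.6442] = Φ(1.038) = 85.0%. Power for at least one outcome, under the assumed rates in step 3, is about 88 to 92%. Restoring 90% for exclusive breastfeeding needs [(2.2414 × 0.6481 + 1.2816 × 0.6442) / 0.10]² = 519.0, so 520 per group, 1040 evaluable and 1040 / 0.9 = 1156 enrolled.

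**5. Rule "exclusive first": single primary, or fixed sequence with exclusive breastfeeding tested first at 5%.** The error rate stays at 5% and power for exclusive breastfeeding stays at 90.7%.

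**The case against.** The strongest reply is that the article already points to exclusive breastfeeding. The hypothesis concerns nothing else, and the Sample size section uses the singular. Under that reading step 5 applies and nothing is lost. In addition, an order of testing or a split of alpha commonly sits in an analysis plan, which is not shown here, so its absence from a journal article is not a fault.

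Both arguments have weight. A reader might infer that the plan lets success on either outcome count as a positive trial. The article does not say so; it states no rule, whether either, both or sequential. A reader might also infer that the stated 5% and 90% cannot both hold. That does not follow: the 90% is stated for exclusive breastfeeding at 25% against 35%, it reproduces, and both figures hold if that outcome decides the trial or is tested first. Even with a Bonferroni split, power for at least one outcome can reach 90% under some assumed rates.

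What remains is not an omission. Two sections name two primary outcomes without rank, and another names one. An unseen analysis plan can order the tests, but it does not remove that disagreement from the published protocol.

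**Conclusion.** The point stands in conditional form. The Abstract and the Primary outcomes section conflict with the hypothesis and the Sample size section on which outcome decides the trial.

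The size depends on the rule: a family-wise error of about 7 to 10% under "either", joint power of roughly 81 to 88% under "both", and 85.0% power for exclusive breastfeeding under a Bonferroni split. None of these losses arises if exclusive breastfeeding is the single or first-tested primary. Only the 90.7% and 85.0% rest wholly on the article's own inputs. The other figures need full-breastfeeding rates, effects or correlations that it does not give; in particular, a gain in full breastfeeding smaller than the assumed 10 points would lower joint power further.

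This should be fixed. It does not undermine the design, because the existing sample size already supports the simplest resolution.

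**What to change.** In the Methods part of the Abstract and in the Primary outcomes section, name exclusive breastfeeding at 6 months as the single primary outcome, in line with the hypothesis and the Sample size section. List full breastfeeding at 6 months as the first key secondary outcome, tested at two-sided 5% only if exclusive breastfeeding is significant. Make the change before any unblinded analysis.

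This is a change of wording. It needs no extra participants and keeps both the 5% and the 90.7%. The cost is that no stand-alone confirmatory claim on full breastfeeding can be made if exclusive breastfeeding is not significant.

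If the investigators do want two primary outcomes, they should state the success rule, give an expected rate and effect for full breastfeeding, and size for that rule. A Bonferroni split that keeps 90% power for exclusive breastfeeding would take about 1156 enrolled instead of 1000.
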